##### Secondary Analyses

In order to investigate associations between parent satisfaction with FCC practices and parent, as well as infant outcomes, we will use multilevel models with PCICU as the level two factor. Such models account for shared exposure to unit characteristics, causing families within a unit to be more similar (to an unknown extent) compared to families from different units.

For the analysis of outcomes on the parent level, we will enter parent satisfaction with FCC as independent variable. Measures of parent well-being (specifically, symptoms of anxiety, depression, stress and parenting stress) will be entered as dependent variables. Extended models will be built to account for potential effects of infant characteristics (e.g., age and gender), medical variables (e.g., duration of stay at hospital, complexity of disease), as well as socio-demographic variables (e.g., employment status, ethnicity or professional background).

For each measure of parent well-being (symptoms of anxiety, depression, stress and parenting stress), a series of multilevel models is estimated. Each model in the set has incremental complexity. All models will be estimated using Restricted Maximum Likelihood, defining the covariance structure through variance components, and using the Huber- White sandwich estimator for the standard errors (50, 51).

For *each* parent well-being measure separately, the series of hypothesis confirming models is outlined below:

1) Model 1 estimates the unconditional means model for the parent well-being score.2) Model 2 estimates the conditional means model, adjusting for infant characteristics, medical and socio-demographic variables.3) Model 3 estimates the random intercept for the fixed slope association between FCC satisfaction and parent well-being, adjusted for infant characteristics, medical and socio-demographic characteristics.4) Model 4 estimates the random intercept and random slope for the association between FCC satisfaction and parent well-being, adjusted for infant characteristics, medical and socio-demographic characteristics.

For the analysis of outcomes on the child level, we will enter parent satisfaction with FCC as independent variable. Measures of infant well-being (specifically, mental and physical well-being as rated by the parents) will be entered as dependent variables. Extended models will explore potential effects of infant characteristics (e.g., age and gender), medical variables (e.g., duration of stay at hospital, complexity of disease), as well as socio-demographic variables (e.g., employment status, ethnicity or professional background). Two series of models are estimated for child well-being (parent-rated physical and parent-rated mental well-being). Similar to above analysis, each model in the set has incremental complexity and all models will be estimated using Restricted Maximum Likelihood, defining the covariance structure through variance components, and using the Huber-White sandwich estimator for the standard errors.

For each child well-being measure separately, the series of hypothesis generating models is outlined below:

1) Model 1 estimates the unconditional means model for the child well-being2) Model 2 estimates the conditional means model, adjusting for infant characteristics, medical and socio-demographic variables.3) Model 3 estimates the random intercept for the fixed slope association between FCC satisfaction and child well-being, mutually adjusted and adjusted for infant characteristics, medical and socio-demographic variables.4) Model 4 estimates the random intercept and random slope for the association between FCC satisfaction and child well-being, adjusted for infant characteristics, medical and socio-demographic variables.

In all series of models, the change in model deviance between subsequently nested models is evaluated at a 5% significance level using the Likelihood Ratio Test.

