## Methods and Analysis

### Design

This two-center cross-sectional study will be conducted at two PCICUs of two specialized pediatric cardiac centers in Germany (Berlin, Bad Oeynhausen).

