### Statistical Analyses

#### Power Analysis and Sample Size

Given the annual number of infants with congenital heart disease at the PCICUs of both centers, an inclusion of *N* = 2 × 140 families (140 families per center) is the maximum achievable number in the data collection period of 1 year. A power analysis was performed using G^*^Power for F-test for multivariate ANOVAs and in R for multilevel modeling using the R package “powerlmm.” Primary analyses are hypothesis generating. Secondary analyses are hypothesis confirming for variables on the parent level and hypothesis generating for variables on the child level. Effect sizes for our patient and age group could not be inferred from earlier studies or meta-analyses.

With an alpha level of 5%, a power of 0.80 and an upper bound total sample size of *N* = 2 × 140, the minimum effect size required for statistical detection in an ANOVA is Cohen's *d* = 0.34. This is considered to be a small-to-medium effect size. That same effect size would lead to an estimated power of 74% in a multilevel model with an alpha of 5%, and a total sample size of *n* = 2 × 140, assuming an intraclass correlation of 0.40, and 5,000 simulation runs. The minimum detectable multilevel effect size with a power of 0.80 is Cohen's *d* = 0.37.

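### Two PCICUs cannot support a random level-two factor: Model 4 is not usefully estimable, a unit-clustered sandwich would be degenerate, and the REML likelihood ratio test of FCC satisfaction is not valid as written

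*Protocol article*

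**What the plan says.** The Design section fixes the number of units: "This two-center cross-sectional study will be conducted at two PCICUs of two specialized pediatric cardiac centers in Germany". For the associations of parent satisfaction with family-centered care (FCC) with parent and infant outcomes, Secondary Analyses states "we will use multilevel models with PCICU as the level two factor". On estimation it says "All models will be estimated using Restricted Maximum Likelihood, defining the covariance structure through variance components", together with a Huber-White "sandwich estimator for the standard errors". The child-level series repeats this.

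The model series runs from an unconditional means model (Model 1), through covariates (Model 2), to a fixed FCC slope with a random intercept (Model 3). It ends with "Model 4 estimates the random intercept and random slope for the association between FCC satisfaction and parent well-being". Successive models are compared as follows: "the change in model deviance between subsequently nested models is evaluated at a 5% significance level using the Likelihood Ratio Test".

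On status, Power Analysis and Sample Size says "Secondary analyses are hypothesis confirming for variables on the parent level and hypothesis generating for variables on the child level". The article does not state the level at which the sandwich is clustered, any small-sample correction, or the reference distribution. It nowhere acknowledges the limit set by having two units.

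**The concern.** A random effect treats the units as a sample from which a variance is estimated. Two units supply one contrast, and so one degree of freedom, for the intercept variance, and one more for the slope variance in Model 4. When the intercept variance is estimated as zero, the fitted model no longer adjusts for center, and the FCC slope can mix within-center and between-center differences.

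The usual reading of a sandwich in a multilevel model is that it is clustered on the level-two unit. With an intercept in the model and two clusters, the two cluster score vectors sum to zero, so the middle matrix of the sandwich has rank 1. Standard errors from it are erratic and typically far too small.

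The third problem is the test of the FCC association itself, Model 3 against Model 2. These models differ in a fixed effect, and REML deviances are not comparable across different fixed-effect designs.

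At stake are the four parent-level associations (anxiety, depression, stress, parenting stress), which are the study's only confirmatory claims.

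**Working it through.** **Inputs from the article.** Two PCICUs (Design); 140 families per center, alpha 5%, power 0.80, intraclass correlation (ICC) 0.40 (Power Analysis and Sample Size); REML, sandwich and Models 1-4, and the likelihood ratio test at 5% (Secondary Analyses).

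**Assumptions.** Two-sided tests, normal errors, no missing data. The ICCs of 0 and 0.05, the eight covariates used in some simulations, the scale SDs in step 4 and the slope SDs in step 5 are illustrative.

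**1. The plan's own figure.** The article gives no type I error rate for these tests. Its ANOVA minimum detectable effect does reproduce: (1.960 + 0.842) x sqrt(2/140) = 0.335 (0.336 with the t distribution), against the printed 0.34. Power at d = 0.34 is 0.81.

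**2. Intercept variance estimated as zero.** With two equal groups this happens when the between-center F ratio is below 1. That ratio is distributed as (1 + 140 x ICC/(1 - ICC)) times F(1, 278), so P(zero) = P(|t| < 1/sqrt(1 + 140 x ICC/(1 - ICC))) on 278 df.

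| ICC | 1 + 140 x ICC/(1 - ICC) | P(zero), formula | P(zero), simulated |
|---|---|---|---|
| 0 | 1.0 | 68% | 70% |
| 0.05 | 8.37 | 27% | 28% |
| 0.40 | 94.3 | 8% | 8-9% |

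**3. Sandwich clustered on PCICU.** For two equal clusters and a true slope of zero, the uncorrected statistic behaves as sqrt(2) times a Cauchy variable. Multiplying the variance by G/(G - 1) = 2 makes it Cauchy, that is t with 1 df. For critical value c:

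- uncorrected: P(reject) = 1 - (2/pi) x atan(c/sqrt(2))
- corrected: P(reject) = 1 - (2/pi) x atan(c)

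| Form | Critical value | Formula | Simulated, 2 x 140 |
|---|---|---|---|
| Unit-clustered, uncorrected | 1.96 | 39.8% | 40-41% |
| Unit-clustered, corrected | 1.96 | 30.0% | 30-31% |
| Unit-clustered, corrected, t(1) | 12.7 | 5.0% | 4.8-5.3% |
| Family-level sandwich | 1.96 | - | 5.3-5.7% |
| Model-based Wald | 1.96 | - | 4.8-5.2% |
| Likelihood ratio test under ML | 3.84 | - | 5.0-5.4% |
| Center as fixed effect, t test | t | - | 4.8-5.1% |

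The simulations fitted a REML random-intercept model with a slope common to both centers, 4,000 runs per setting. A separate simulation (1,500 runs per setting, eight covariates, ICC 0, 0.05 and 0.40) gave 39-40% for the uncorrected form and 5-6% for the fixed-center regression. With an uneven split of 200/80 the uncorrected form rejects 44%.

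**4. Likelihood ratio test on REML fits.** Adding one fixed slope changes the REML deviance by approximately F + ln(2 x pi) - ln(Sxx/s2). Here Sxx is the sum of squares of the satisfaction score and s2 the residual variance. The last term depends on the units of measurement. With Sxx = 280 x SDx^2 and s2 = 0.6 x SDy^2, the F needed to reject is 3.841 - 1.838 + ln(Sxx/s2):

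- SDx 1, SDy 1: ln(466.7) = 6.146; F needed 8.15; true null rejected 0.4%
- SDx 20, SDy 8: F needed 9.98; rejected 0.2%
- SDx 0.5, SDy 5: F needed 3.54; rejected 6.0%
- SDx 0.3, SDy 8: F needed 1.58; rejected 21%

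The same data scored on a different scale would give a different decision.

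**5. Slopes that differ between centers.** If center slopes vary around a mean of zero with SD 0.1 or 0.2, the fixed-slope model-based test, the ML likelihood ratio test and fixed-center regression all reject about 29% or 55% respectively. They detect a slope that is real in these two units but is not the mean over units in general. Two units cannot supply the variance needed for that wider claim.

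**The case against.** A reader might infer that the plan's confirmatory tests reject a true null about 40% of the time, or that all their p-values and intervals are invalid. The article does not support that. The 40% belongs to one form of sandwich (clustered on PCICU, uncorrected, normal reference), and the article fixes none of these choices. A condensed article may leave them to a fuller plan, and the wording does not exclude a family-level sandwich. Across the forms checked, the rate runs from about 5% to 44%.

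The decision rule that the article names is the likelihood ratio test, which does not use the sandwich. Under ML with a common slope it holds about 5% in this two-unit model. Two units alone therefore do not invalidate a test of the family-level slope.

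Other limits also stand. The 70% rate of zero intercept variance belongs to ICC 0, where there is no center effect to adjust for; at the plan's ICC of 0.40 it is 8-9%, and no resulting bias was computed. Model 4 addresses slope heterogeneity, whereas the hypothesis in the Introduction is the Model 3 association, so Model 4's weakness does not by itself undo the four associations.

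These limits do not rescue the plan. The random slope over two units is a stated choice, and so is REML for every model. The named test escapes the sandwich problem but, as written, runs into the REML problem.

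**Conclusion.** The concern holds in a conditional form. What the article fixes is enough to establish two defects: a random-slope variance resting on one degree of freedom, and a comparison of Model 2 with Model 3 on REML deviances that is not valid. Depending on assumed measurement scales, that comparison rejects a true null between about 0.2% and 21% of the time.

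The third defect depends on what the article leaves open. If the sandwich is clustered on PCICU, the robust tests reject about 40% uncorrected and 30% corrected with a normal reference. A t(1) reference restores 5%, but its critical value of 12.7 leaves almost no power. If the sandwich is at family level, the rate is 5-6%.

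Neither planned route to a p-value is thus assured to hold 5%. All figures assume normal errors and complete data, and the rates near 5% also assume one slope common to both centers. Because the only confirmatory claims rest on these models, this should be settled before analysis.

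**What to change.** - Enter PCICU as a fixed effect in every model. Primary Analyses already treats unit as a fixed between-subjects factor, so the two parts of the plan would then agree.
- Replace Model 4 by a fixed unit-by-FCC-satisfaction interaction (1 df).
- Use model-based or family-level heteroskedasticity-robust standard errors, not errors clustered on two units, and name the form and reference distribution.
- Test fixed effects, including Model 3 against Model 2, with ML fits or an ordinary t or F test.
- State that inference is conditional on these two units.

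The cost is wording and simpler code, with no new data. The downside is that no between-unit variance is estimated, which two units could not provide anyway.

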#### Parent Satisfaction With FCC Practices

We will use the EMpowerment of PArents in The Intensive Care-30 Questionnaire (EMPATHIC-30) (36). It is a self-report instrument consisting of 30 statements and assesses satisfaction with experiences at the ICU. The questionnaire is divided into five domains: information (five items), care and cure (eight items), parental participation (six items), organization (five items) and professional attitude (six items). Responses are given on a six-point scoring scale ranging from 1 (“certainly no”) to 6 (“certainly yes”). A separate box “not applicable” is available for all statements. The questionnaire was translated and culturally adapted for use in German-speaking populations by Nagl-Cupal and Lippoldt (37). Latour and colleagues reported a Cronbach's a of 0.93 on the full scale and Cronbach's a ranging from 0.73 to 0.81 on the domain level (36).

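### With two units, the 5% likelihood ratio test of Model 3 against Model 4 runs at about 0 to 1.4%, and its result depends on where the satisfaction score has its zero

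*Protocol article*

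**What the plan says.** All of this is in the protocol article.

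- **Secondary Analyses, level two:** "we will use multilevel models with PCICU as the level two factor". There are two such units.
- **Estimation and covariance:** "All models will be estimated using Restricted Maximum Likelihood", "defining the covariance structure through variance components". The same wording governs the child-level models.
- **The two models compared:** "Model 3 estimates the random intercept for the fixed slope association between FCC satisfaction and parent well-being"; "Model 4 estimates the random intercept and random slope for the association between FCC satisfaction and parent well-being". Both are adjusted for the same infant, medical and socio-demographic variables.
- **The test:** "the change in model deviance between subsequently nested models is evaluated at a 5% significance level using the Likelihood Ratio Test". No reference distribution is named.
- **The predictor (Parent Satisfaction With FCC Practices):** "Responses are given on a six-point scoring scale ranging from 1", up to 6. Satisfaction enters as the independent variable; centring is neither stated nor excluded.

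The step occurs in six series: anxiety, depression, stress and parenting stress for the parents, and physical and mental well-being for the child.

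**The concern.** Model 4 is the only step that asks whether the satisfaction slope is the same in both units. A non-significant result will naturally be read as support for a common slope. Two features make that reading unsafe.

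1. The null value of a variance, zero, is the edge of its range, and here the variance is estimated from two units. The usual chi-square critical value is then too strict, and real differences are missed.
2. In its usual meaning, a variance-components structure gives each random effect a variance and no covariance. Intercept and slope are thus assumed uncorrelated at the point where the score equals zero. Moving that point changes the model, and zero lies outside a 1 to 6 scale. The same data can give different answers for a raw and a centred score.

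**Working it through.** **The plan's own figures (Power Analysis and Sample Size).** With 140 per center and d = 0.34, the standardised difference is 0.34/sqrt(2/140) = 2.845, and power is Phi(2.845 - 1.960) = 0.81. This agrees with the stated minimum of 0.34 at 80%. For the multilevel model, 74% power at 0.34 implies a standard error of 0.131 and a minimum detectable d of 0.366 at 80%, consistent with the stated 0.37. The article gives no figure for the Model 3 to 4 test except its 5% level.

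**Inputs.** From the article: two units, 140 families each, REML, zero intercept-slope covariance, 5% level, ICC 0.40. Assumed: residual SD 1, no covariates, and satisfaction mean and SD of 5.0 and 0.7 (range 4.5/1.0 to 5.5/0.5) or 5.2 and 0.6. The reference is taken as chi-square with 1 df (critical value 3.841), because Model 4 adds one parameter.

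**Level, centred score.** Let w be the squared slope difference between units divided by its sampling variance. With two units and the residual variance treated as known, the statistic is w - 1 - ln w for w > 1, and 0 otherwise. It reaches 3.841 at w = 6.75, and P(chi-square(1) > 6.75) = 0.94%. A boundary null with many units would give about 2.5%; having only two units accounts for the rest of the shortfall.

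**Level, other codings.** Exact two-unit REML likelihood, 20,000 data sets, mean 5.0, SD 0.7, no slope difference:

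| Coding | ICC 0 | ICC 0.10 | ICC 0.40 |
|---|---|---|---|
| Raw (zero at 0) | 0.01% | 0.2% | 1.0% |
| Recoded (zero at 1) | 0.02% | 0.4% | 1.2% |
| Mean-centred | 0.9% | 0.9% | 0.9% |
| Free covariance, chi-square(2) | 0.5% | 0.9% | 1.2% |

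Over all settings tried, the rate runs from about 0 to 1.4%.

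**Dependence on the zero, one data set.** Take unit slopes that differ by 0.5 residual SD per point, with lines crossing at the mean of 5.0 and SD 0.7. The sampling variance of the slope difference is 2/(140 x 0.49) = 0.0292, so w = 0.25/0.0292 = 8.6 and the centred statistic is about 8.6 - 1 - 2.15 = 5.4. The exact value, with the residual variance estimated, is 5.35. For the same data:

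| Zero placed at | 0 | 1 | 3.5 | 5 | 6 |
|---|---|---|---|---|---|
| Statistic | 0.00 | 0.00 | 0.97 | 5.35 | 1.78 |

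Only the centred coding exceeds 3.841. The reason is that lines crossing near 5 have strongly negatively correlated intercepts and slopes at 0. With slope variance 0.1 and ICC 0.10, the intercept variance at 0 is 0.111 + 25 x 0.1 = 2.611 and the covariance is -5 x 0.1 = -0.5. The correlation is -0.5/sqrt(2.611 x 0.1) = -0.98, which Model 4 excludes.

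**Power (mean 5.2, SD 0.6, residual SD 1, slope difference 0.4 SD per SD).**

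| Unit difference at average satisfaction | Raw | Centred |
|---|---|---|
| None | about 29% | about 76% |
| Drawn from ICC 0.40 | about 59% | about 77% |

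At ICC 0.40 the two codings disagree in about 21% of data sets. The centred figure follows from the closed form: 0.4/sqrt(2/140) = 3.35, sqrt(6.75) = 2.60, Phi(3.35 - 2.60) = 77%. A 1-df fixed interaction has Phi(3.35 - 1.96) = 92%. Even with the best coding, the planned test gives up about 15 points of power (92 - 77).

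**The case against.** **Centring may be intended.** The article is silent, and a condensed article may leave such a detail to an analysis plan. This stands: one may not conclude that the score is uncentred. But the article itself fixes the covariance structure, and under that structure the test has no defined answer until the zero is fixed. The loss of the 5% level needs no assumption about centring.

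**The two faults are easily run together.** A reader might infer that the zero covariance or an uncentred score causes the loss of the 5% level. The figures do not support this: the level is 0.94% with a centred score and 0.5 to 1.2% with a free covariance.

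**Equal unit means are an unfavourable case.** True, and the article assumes an ICC of 0.40. There the gap narrows from 29% against 76% to 59% against 77%. With a fixed unit difference of 1 SD it depends on the sign: 77% against 78% one way, 58% against 76% the other. At a slope difference of 0.6 with equal unit means it is 85% against 99%. The dependence shrinks, but remains in most of these settings.

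**The consequence is limited.** A reader might infer that the confirmatory findings are invalid or that false positives are inflated. Neither follows. The hypothesised association enters at Model 2 to 3, no stated hypothesis concerns a slope difference between units, and the error is conservative.

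**Conclusion.** The point holds as two separate faults in the Model 3 to 4 step.

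1. The test does not deliver its stated 5%. Against the ordinary chi-square reference it rejects in about 0 to 1.4% of data sets when the slopes are equal. The cause is a boundary null with two units, and centring does not cure it.
2. Under the stated covariance structure the result depends on the zero of a score whose coding is not given. For a slope difference of 0.4 SD per SD the gap between raw and centred coding is about 47 percentage points with equal unit means (29% against 76%) and about 18 at ICC 0.40 (59% against 77%).

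The power figures rest on the assumed score mean and SD, residual SD 1 and no covariates. The 0.94% level for the centred score does not depend on the assumed mean, SD or ICC. The harm is a missed difference between the two units, and a non-significant Model 4 that is read as evidence of a common slope.

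**What to change.** In all six series, replace the Model 3 to 4 likelihood ratio test by a fixed satisfaction-by-unit interaction on 1 df, with a fixed unit main effect, and report the estimate with its 95% CI. This test does not depend on the score's zero, so it needs no centring rule. It holds its level and has about 92% power at 0.4 under the assumptions above. Its standard error should be the ordinary one or one robust at the family level, since a sandwich clustered on two units is not usable for this term.

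If the random slope is kept, either centre the score at the grand mean or allow the intercept-slope covariance, and calibrate the test by parametric bootstrap for two units. Centring at each unit's mean is unnecessary, and it would take the between-unit part of satisfaction out of Model 3.

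The cost is analysis wording only; no data or sample size change. The downside is that the interaction describes these two units and does not generalise to other units.

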##### Preliminary Analyses

Given the expected sample size of 140 families for each PCICU, the Central Limit Theorem applies, rendering the assumption of normality in the predictor and/or outcome variables redundant. We will assess linearity of the association between parental FCC satisfaction and FCC adherence. Furthermore, we will assess equality of variances between centers on FCC satisfaction and FCC adherence. Missing data, if any, are evaluated for their origin, being Missing Completely At Random (MCAR), or either Missing At Random (MAR) or Not Missing At Random (NMAR) using Little's MCAR test to probe for the risk of bias in the main analyses (48). If missing values are missing completely at random, missing values are handled within the multilevel models through restricted maximum likelihood estimation. If data are MAR/NMAR, data will be multiply imputed before the main analyses (49). Results for all following analyses will be pooled over imputed datasets. Furthermore, we will report descriptive statistics of and analyze differences between centers concerning socio-demographic characteristics of the primary caregiver and infant medical characteristics.

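### The plan's sandwich standard errors never enter its only stated decision rule, so the confirmatory satisfaction slope is not protected if residual spread varies with satisfaction

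*Protocol article*

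**What the plan says.** All places are in the protocol article, under Statistical Analyses.

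- **Estimation and standard errors (Secondary Analyses).** "All models will be estimated using Restricted Maximum Likelihood", with variance components for the covariance structure and "using the Huber- White sandwich estimator for the standard errors". The same specification is repeated for the child outcomes.
- **Decision rule (end of Secondary Analyses).** "In all series of models, the change in model deviance between subsequently nested models is evaluated at a 5% significance level", by likelihood ratio test. No Wald test or confidence interval based on the sandwich standard error is named as the basis for a decision.
- **Status (Power Analysis and Sample Size).** "Secondary analyses are hypothesis confirming for variables on the parent level and hypothesis generating for variables on the child level".
- **Assumptions (Preliminary Analyses).** The Central Limit Theorem is cited as "rendering the assumption of normality in the predictor and/or outcome variables redundant". The only variance check compares the two centers, on satisfaction and on adherence.

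**The concern.** Choosing a sandwich estimator means not wanting to rely on the model-based variance. The decision rule relies on it entirely, because the deviance change from Model 2 to Model 3 assumes one constant residual variance. The test and the reported robust standard error can then point in different directions for the same slope, and the article does not say which one counts.

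Nothing else in the plan covers the gap. The Central Limit Theorem argument concerns non-normality, not a residual variance that changes along the predictor. Equality of variance between centers is a different question from equality across levels of satisfaction.

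At stake is the false-positive rate of the parent-level slope, the only hypothesis the study calls confirming. If satisfaction scores bunch near the top of the scale, dissatisfied families have high leverage. Larger residual spread among them makes the model-based variance of the slope too small.

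**Working it through.** **1. The plan's own figures.** With 140 per center and two-sided 5% (sidedness is assumed), the noncentral t gives 80.9% power at d = 0.34 and a minimum detectable d of 0.336. The stated 0.34 is reproduced. The multilevel pair is consistent: 0.34 × (1.960 + 0.842)/(1.960 + 0.643) = 0.366, against 0.37 stated. The multilevel power simulation itself cannot be rerun from the inputs given. These figures take a true 5% level for granted.

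**2. How far the level can move.** Let R be the true variance of the slope divided by the model-based variance. In large samples

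R = E[(x − μ)²σ²(x)] / {Var(x) · E[σ²(x)]}, and the rejection rate under the null is 2 × [1 − Φ(1.96/√R)].

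Constant σ² gives R = 1 and 5%, whatever the shape of x. A rate of 13% needs R = 1.68; 23% needs R = 2.67.

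**3. A worked family of gradients (assumed).** Satisfaction is x = 6 − g with g ~ Gamma(shape 1.6, scale 0.5), clipped to 1-6: mean 5.2, SD 0.63. The slope is zero and the residual SD is linear in g. Ignoring the clipping, g has mean 0.8 and central moments 0.4, 0.4 and 1.08. Let b be the SD increase per point of satisfaction lost and m the SD at the mean. Then

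R = (0.4m² + 0.8mb + 1.08b²) / [0.4(m² + 0.4b²)].

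For SD 0.8 at score 6 and 1.4 at score 4: b = 0.3, m = 0.8 + 0.8 × 0.3 = 1.04, so R = 0.779/0.447 = 1.74 and the rate is 13.8%.

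The simulations used 2 × 140 families, normal errors, ML fits with unit as a fixed effect, and 4,000 runs per setting. Ranges come from repeat runs.

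| Residual SD, score 6 to score 4 | R | Formula | Simulated likelihood ratio test | Simulated HC3 t-test |
|---|---|---|---|---|
| constant | 1.00 | 5.0% | 4.9-5.2% | 5.1-5.4% |
| 0.9 to 1.1 | 1.23 | 7.7% | 6.7% | 4.7% |
| 0.9 to 1.2 | 1.34 | 9.1% | 9.8% | 5.7% |
| 0.8 to 1.4 | 1.74 | 13.8% | 13.2-14.4% | 5.1-5.9% |
| 0.6 to 1.6 | 2.43 | 20.9% | 19.0-19.9% | 5.0-5.5% |
| 0.5 to 2.0 | 3.05 | 26.2% | 23.5-25.7% | 5.2-6.1% |

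The two tests disagree in 7.7% of data sets at 0.8 to 1.4, and in 19.6% at 0.5 to 2.0.

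**4. Other assumed scenarios.** Here the likelihood ratio test comes from ML fits with a random unit intercept. Treating unit as fixed made no material difference when both were fitted to the same data.

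- Bounded, skewed outcome unrelated to satisfaction: 4.5% and 5.4% for DASS-like 0-21 scores, 4.8% for a PSS-like score. There is no inflation.
- Bounded 0-21 score, flat mean, dispersion larger at low satisfaction (mild to extreme): 6.7%, 8.6%, 13.1%; HC3 5.4%, 5.9%, 6.4%.
- Unequal spread arising through an adjusted covariate correlated with satisfaction: 6.5%, 7.2%, 12.4%; HC3 5.5%, 4.7%, 7.8%.
- Continuous score, SD multiplied by exp(k) per SD of lower satisfaction: 8.7% (k = 0.1), 16.3% (0.2), 24.7% (0.3), and 38.6% at k = 0.5; HC3 5.2-6.2%.

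**5. Level of the sandwich.** Clustered on the two units with a z reference, the Wald test rejects a true null in about 39-44% of runs across the scenarios in step 4.

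**The case against.** The strongest counter-argument concerns cause. A reader might infer that bounded, skewed scales by themselves push the 5% test to 13-23%. They do not: step 4 shows about 5% when the outcome is bounded and skewed but unrelated to satisfaction. A floor effect does not rescue that inference. Satisfied parents crowd the distress floor only if their mean distress is lower, which is the alternative hypothesis. With a zero slope, all satisfaction levels sit equally close to the floor. All the inflation comes from an imposed variance gradient, and the document neither states nor implies one. This objection stands in full, and it is why the sizes here are conditional.

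Second, the test simulated is not literally the one written. The article uses REML throughout, and REML deviances are not comparable between models with different fixed effects, as in Models 1 to 2 and 2 to 3. Taken literally, the rule gave 0.6%, 5.5% and 8.3% with no association at all, depending on the outcome's scale, and between 0.6% and 29% over all scenarios. That is a separate defect. Refitting by ML with unit fixed cures it and leaves the present mismatch untouched.

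Third, a condensed article may leave coefficient reporting to the full plan, and the deviance rule also covers the exploratory child models. That is fair as far as reporting goes. But the article does state a decision rule at 5%, applies it to the confirming models, and names no other.

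Fourth, a fixed-unit regression departs from the multilevel series and must say what becomes of Model 4. The fix does so.

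**Conclusion.** The mismatch is on the page: robust standard errors are specified, and the only stated test ignores them. Whether it does harm depends on something the documents do not tell us. With constant residual spread the ML likelihood ratio test holds about 5%, however bounded or skewed the scales are. If spread changes with satisfaction, illustrative rates are about 7-8% for a mild gradient, 7-13% for bounded 0-21 scores and up to about 25% for strong gradients on a continuous score; more extreme gradients go higher. These rates assume 280 families, a zero slope, a ceiling-skewed satisfaction score and ML fits. They are scenarios, not properties of this plan, and no single figure should be quoted as its error rate. The point is worth correcting before analysis because the affected test is the confirmatory one and the remedy is already half written into the plan.

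**What to change.** Adopt one decision rule. For each parent outcome, test the satisfaction slope in the adjusted model (Model 3, with unit as a fixed effect because there are only two units) by a Wald t-test using family-level HC3 standard errors. Report the matching 95% confidence interval.

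State the level of the sandwich explicitly as the family. Do not cluster it on the two units.

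Keep deviance changes, including Model 4 against Model 3, as descriptive information on fit, and use ML fits wherever the fixed effects differ.

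The cost is wording in the analysis plan and standard software. If spread is in fact constant, the loss is about one point of power (79.7% against 80.7% in simulation). HC3 is not perfect: it held 4.7-6.4% in all but one of the scenarios in step 4, and reached 7.8% in the strongest confounded one, where the likelihood ratio test gave 12.4%.
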